#### Blood measures

Fasted venous blood samples (54 mL) were collected by a credentialed phlebotomist at the in-person visit. Blood parameters that will be measured are shown in Table 4. Genetic variation at 1.8 million markers (e.g., single-nucleotide polymorphisms) will be measured from serum blood samples using Illumina’s Infinium Global Diversity Array genotyping platform. We chose this array, along with our downstream imputation pipeline, because it is used by and can be harmonized with the All of Us dataset, uses a multiancestry array design, has content breadth, and can be imputed to a diverse genome reference. Zinc protoporphyrin was measured immediately after collection using the ProtoFluor Z Analyzer (Helena Laboratories). Complete blood cell counts were analyzed in whole blood within 48 h of blood collection. Plasma, serum, and whole blood were divided into aliquots in prespecified tubes to limit the occurrence of freeze–thaw cycles and shipped on dry ice for storage at −80°C before analysis. After initial assays are completed, the remaining blood will be archived and retained for future use.

**TABLE 4 tbl4:** Blood biomarkers assessed in the Military Health and Nutrition Examination Study

Measures of anemia and iron status	Nutrient status and electrolytes	Hormone status	Biomarkers of stress	Cardiometabolic health and inflammation
Hemoglobin	Calcium	Total testosterone	Cortisol	Glucose
Hematocrit	25-OH vitamin D	Estradiol	DHEAS	Hemoglobin A1c
Red cell distribution width	Vitamin D–binding protein	Sex hormone–binding globulin	Creatine phosphokinase	Insulin
Mean cell hemoglobin concentration	Magnesium	Thyroid-stimulating hormone		Lipids (total cholesterol, non-HDL-C, LDL-C, HDL-C, and triglycerides)
Mean cell hemoglobin	Chloride	Triiodothyronine		Amylase
Mean cell volume	Sodium	Thyroxine		Liver enzymes
Ferritin	Phosphorus	PTH		hsCRP
sTfR	Potassium			α-1-Acid glycoprotein
Iron	Vitamin B-12			Complete blood cell count
TIBC	Folate			Albumin
Hepcidin	RBC fatty acids			Total protein
Erythropoietin	Retinol binding protein			Blood urea nitrogen
Erythroferrone				Creatinine
Zinc protoporphyrin				

Abbreviations: DHEAS, dehydroepiandrosterone sulfate; hsCRP, high-sensitivity C-reactive protein; PTH, parathyroid hormone; RBC, red blood cell; sTfR, soluble transferrin receptor; TIBC, total iron–binding capacity.

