**Methods:**

MHANES recruited Soldiers (n = 648) from Army installations across the United States. Participants attended an in-person visit to complete a 24-h dietary recall and questionnaires regarding demographics, physical and mental health, physical activity and performance, and dietary supplement and medication use. Height, weight, blood pressure, resting heart rate variability, physical activity, sleep, resting metabolic rate, hemoglobin mass, and blood volume were measured. Body composition was assessed using bioelectrical impedance, 3-dimensional body imaging, dual-energy X-ray absorptiometry, and circumference measurements. Blood and urine samples were collected to measure biomarkers of nutritional status, health, and genetics. Stool samples were collected to assess microbial diversity and composition. A second 24-h dietary recall was administered 3 to 10 d after the in-person visit.

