## Trial aim

The aim of MHANES is to provide comprehensive information on nutritional, biochemical, and medical status and lifestyle behaviors of active-duty Army Soldiers by assessing dietary intake, cardiometabolic health, body composition, biomarkers of nutritional status and health, mental well-being, sleep, physical activity, injury prevalence, genetics, gut microbiome composition, and physical performance in a large representative sample of Army Soldiers.

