Biospecimens are processed using standardized protocols and tracked using unique participant identifiers. Whole blood, plasma, serum, urine, and stool samples were divided into aliquots in prespecified tubes to minimize freeze–thaw cycles before long-term storage. Laboratory analyses are centralized to minimize interlaboratory variability. Instrument calibration and quality control procedures are conducted according to the manufacturer’s recommendations.

Before analysis, datasets will undergo centralized harmonization and cleaning procedures, including standardized variable naming conventions, coding dictionaries, review of outliers and implausible values, and cross-site consistency checks.

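### Array genotyping is specified from serum, a cell-free fraction and a poor source of genomic DNA, although whole blood is aliquoted and stored separately

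*Protocol article*

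**What the plan says.** Under Blood measures, the protocol article plans to assay "Genetic variation at 1.8 million markers" on a commercial genotyping array and says that these "will be measured from serum blood samples using" that platform. It explains the choice of array by harmonization with an external multi-ancestry dataset and by a downstream imputation step.

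The same section describes what was kept: "Plasma, serum, and whole blood were divided into aliquots in prespecified tubes", with shipment on dry ice and storage at −80°C before analysis. It adds that "After initial assays are completed, the remaining blood will be archived and retained for future use".

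The section Data quality control and management gives the same separation of fractions: "Whole blood, plasma, serum, urine, and stool samples were divided into aliquots in prespecified tubes".

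Genetics is a stated study domain. The Trial aim lists "injury prevalence, genetics, gut microbiome composition, and physical performance in a large representative sample of Army Soldiers", and the abstract's Objectives also name it.

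**The concern.** Genomic DNA sits in nucleated cells, and serum is the blood fraction from which the cells have been removed. Some DNA remains in it, but in low quantity and in fragments. A genome-wide array followed by imputation depends on adequate DNA and a good call rate, so serum is the wrong fraction to name when a cellular one has been kept.

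Genetics would be affected for as many of the 648 participants as are genotyped. The reasons given for choosing this array, harmonization and imputation, also depend on genotype quality. The article does not merely leave out a laboratory detail here: it names a specimen, and laboratories and later data users may rely on it.

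**Working it through.** No formula applies and there is no figure in the plan to reproduce. The check is a comparison of every place where the article names a blood fraction or genetics.

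1. **Specimen named for genotyping.** Blood measures says serum ("will be measured from serum blood samples using"). This is the only place where the article ties genotyping to a particular blood fraction.

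2. **Does another section correct it?** The abstract's Methods say "Blood and urine samples were collected to measure biomarkers of nutritional status, health, and genetics", with no fraction named. The abstract's Objectives and the Trial aim list genetics without a specimen. The section on the gut microbiome describes extracting and quantifying DNA, but for stool. No section names whole blood, buffy coat or another cellular fraction as the source of participants' DNA.

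3. **Could serum be loose wording for blood in general?** The article does keep the fractions apart elsewhere. Blood measures and Data quality control and management both list whole blood, plasma and serum as separate items, and the cell-based assay is assigned to a cellular specimen: "Complete blood cell counts were analyzed in whole blood within 48 h of blood collection". A reader who takes the article's terms at face value will therefore read serum as serum.

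4. **Is a suitable specimen on hand?** Blood measures has whole blood aliquoted and stored at −80°C, and expects material to remain after the initial assays. The article does not give the anticoagulant, the aliquot volume, or whether another cellular fraction was kept. It follows that a cellular specimen exists, but its suitability for DNA extraction has to be confirmed.

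5. **Is there still time?** Collection ran from August 2024 to February 2026, while genotyping is written in the future tense. On the article's wording, the specimen can still be corrected without a new draw.

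6. **Size.** The upper bound on the number affected is the full sample of 648. The loss per sample cannot be computed: the article gives no DNA yield from serum, no input requirement for the array and no call-rate threshold.

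**The case against.** The strongest reply is that this is a slip of wording and not a design decision. The phrase is an odd one, whole blood is plainly stored, and the abstract speaks only of blood and urine. If the laboratory already intends to extract DNA from whole blood, nothing in the study changes. This may well be so, and it limits the point to a correction. It does not remove it, because serum is the only specimen the article gives and nothing else in the text overrides it.

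A second reply is that the reach is limited. Genetics is one of many domains, the sample size estimate does not rest on it, and the listed analyses do not single it out. That also stands. The point concerns the genetics data only.

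A reader might infer more than the documents support:

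- **That the genetics aim would have no usable DNA.** Serum does hold some DNA, and without yield, input or call-rate figures the supportable statement is a risk, not a certain failure.
- **That extraction would exhaust the serum needed for the Table 4 assays.** No serum volumes or assay requirements are given. The article reports a 54 mL draw and expects blood to be left over.
- **That other assays would use up the whole blood first.** Zinc protoporphyrin was read immediately after collection and cell counts were done within 48 h, so these two do not appear to compete for frozen aliquots. No other competing use is quantified.
- **That failed samples would be missing selectively.** Nothing in the article ties failure to participant characteristics.

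Nor is it a fault that the article sets no call-rate exclusion and no aliquot reserved for DNA. Such details belong in the laboratory manual or analysis plan, and the mention of prespecified tubes suggests that an allocation scheme exists.

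**Conclusion.** The point holds as a correctable misstatement in the methods for a named aim. The article assigns genome-wide genotyping to a cell-free fraction while a cellular one is stored, and following it literally risks inadequate DNA yield and poor call rates. At most all 648 participants' genotypes are affected, and the degree of loss cannot be derived from the documents.

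The conclusion rests on three things: the general fact that serum has had its cells removed; the article's own separation of serum from whole blood; and its future tense, taken to mean that genotyping has not begun. If the intended source was whole blood all along, only the text is at fault. It is worth correcting in either case, because the cost is very small and the sentence governs work still to be done.

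**What to change.** Before genotyping starts, confirm with the laboratory which fraction is the DNA source. Then correct the sentence in Blood measures so that it names genomic DNA extracted from the stored whole-blood aliquots, or from another retained cellular fraction if one exists. If serum is truly intended, state that cell-free DNA is being used and justify it for a genome-wide array with imputation.

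The cost is one query to the laboratory and one corrected sentence, carried over to the full protocol and laboratory manual if they contain the same wording. If the stored whole blood proves suitable, no new collection is needed.

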#### Urinary measures

Participants provided a fasted urine sample (second void of the day). Urine was divided into aliquots in prespecified tubes to limit the occurrence of freeze–thaw cycles and was shipped on dry ice for storage at −80°C before analysis. Iodine, creatinine, and a semiquantitative measure of microalbumin (i.e., the albumin-to-creatinine ratio) will be measured in the urine sample. After initial assays are completed, the remaining urine will be archived and retained for future use.

#### Gut microbiome diversity and composition

Stool samples were collected by participants into collection tubes containing DNA/RNA shield (#R1101; Zymo Research). Participants were instructed to store and transport samples at room temperature and deliver them to study staff within 7 d of collection. Upon receipt by study staff, samples were frozen and shipped at −20°C. Once samples arrived at PBRC, they were stored at −80°C until analysis. Genomic DNA will be extracted using standard bead-based extraction methods and quantified before analysis. Shotgun metagenomic sequencing of extracted DNA will be conducted for taxonomic and functional profiling of the gut microbiome.

#### Psychomotor Vigilance Test (National Aeronautics and Space Administration PVT+)

This is a 5-min test of simple visual reaction time widely used to assess alertness [16]. The test requires volunteers to sustain attention and respond to stimuli presented at random intervals on a computer screen by pressing a button. Parameters recorded include reaction time, premature responses, correct responses, and number of lapses. This test was completed while participants were in the fasted state to minimize the acute effects of dietary intake, caffeine, and nicotine on reaction time.

#### Questionnaires

Questionnaires assessed demographic and lifestyle information, eating behaviors and diet quality, current and past physical and mental health, prescription drug and dietary supplement use, and physical performance on military fitness tests (Table 5). Questionnaires were administered at the in-person visit and required ∼90 to 120 min to complete. Questionnaire data were collected via a tablet device and managed using Research Electronic Data Capture (REDCap) electronic data capture tools at PBRC [17,18].

**TABLE 5 tbl5:** Questionnaires administered in the Military Health and Nutrition Examination Study

Questionnaire/instrument	Domain assessed	Items (no.)	Estimated time (min)	Key variables/outcomes
Lifestyle and Health Questionnaire	Lifestyle behaviors, general health	72	15–20	Tobacco/alcohol use, medical conditions, physical activity behaviors, income
Military Eating Behaviors Survey (MEBS)	Eating behaviors and mediators	133	30–40	Hunger, satiety, cravings, meal patterns, restraint, diet rigidity, emotional eating, food choice, stress, food access
Patient Health Questionnaire (PHQ-9)	Depression	9	2–3	Depression severity score (0–27)
Generalized Anxiety Disorder (GAD-7)	Anxiety	7	2–3	Anxiety severity score (0–21)
Life Events Checklist for DSM-5 (LEC-5)	Trauma exposure	16	3–5	Exposure to traumatic events
Primary Care PTSD Screen for DSM-5 (PC-PTSD-5)	PTSD	5	2–3	PTSD risk (score 0–5)
General Self-Efficacy Scale (GSE)	Self-efficacy	10	2–3	Self-efficacy score (10–40)
Pittsburgh Sleep Quality Index (PSQI)	Sleep quality	19	5–7	Sleep duration, efficiency, disturbances, total sleep score
Connor-Davidson Resilience Scale (CD-RISC)	Resilience	25	5–7	Resilience score (0–100)
Profile of Mood States (POMS 2-A)	Mood states	65	12–15	Tension, depression, anger, vigor, fatigue, confusion, total mood disturbance
Dimensional Obsessive-Compulsive Scale (DOCS)	OCD symptom severity	20	5–7	OCD symptom domains (contamination, symmetry, harm, taboo thoughts)
Injury Questionnaire	Musculoskeletal injury history	∼10–15 (variable)	3–10	Injury type, location, date of injury, severity, cause, and duration
Pain, Enjoyment, General Activity (PEG) Scale	Pain and function	3	1–2	Pain intensity and interference (0–10)
Reproductive Health Questionnaire (females only)	Reproductive health	∼30–40 (variable)	10–15	Menstrual status, contraceptive use, reproductive history

Abbreviations: DSM-5, Diagnostic and Statistical Manual of Mental Disorders, 5th edition; OCD, obsessive-compulsive disorder; PTSD, post-traumatic stress disorder.

#### Lifestyle and Health Questionnaire

Demographic, lifestyle, and health information, including but not limited to age, education, marital status, race/ethnicity, alcohol and tobacco use, food security, and physical activity, was assessed via questionnaire. Reproductive health information was collected from females via a separate questionnaire.

#### Military Eating Behaviors Survey

The Military Eating Behaviors Survey (MEBS) is a validated tool to examine military eating habits and mediators of eating behavior and was administered at the in-person study visit [19]. MEBS has 133 items (43 eating habits; 90 mediating behaviors), with 14 eating habit scales (hunger, satiety, food craving, meal pattern, restraint, diet rigidity, emotional eating, fast/slow eating rate, environmental triggers, situational eating, supplement use, and food choice) and 8 mediating factor scales (body composition strategy, perceived stress, food access, sleep habits, military fitness, physical activity, military body image, and nutrition knowledge).

#### Patient Health Questionnaire-9

The Patient Health Questionnaire-9 (PHQ-9) is a 9-item, self-reported depression questionnaire used by health professionals to identify potential cases of major depressive disorder or other depressive disorders. The PHQ has been shown to be a valid measure of depression severity [20]. This questionnaire identifies feelings over the past 2 wk based on a 4-point scale (ranging from “Not at all” to “Nearly every day”). The PHQ-9 questionnaire is scored from 0 to 27; higher scores represent greater depression severity. For the following question: “Over the last 2 wk, how often have you been bothered by the following problem: Thoughts that you would be better off dead or of hurting yourself in some way?”, if a participant answers “SEVERAL DAYS,” “MORE THAN HALF THE DAYS,” or “NEARLY EVERY DAY,” the individual was referred to the Command’s Behavioral Health Officer or Emergency Medical/Behavioral Health Services.

#### General Anxiety Disorder 7-item scale

Anxiety was assessed with the Generalized Anxiety Disorder 7-item scale (GAD-7), a validated measure of anxiety used to identify anxiety disorders [21]. The GAD-7 is composed of 7 items and is scored from 0 to 21; higher scores represent greater anxiety.

#### The Life Events Checklist for Diagnostic and Statistical Manual of Mental Disorders, 5th edition

The Life Events Checklist for Diagnostic and Statistical Manual of Mental Disorders, 5th edition (LEC-5) was administered to participants to screen for exposure to potentially traumatic events [22]. The LEC-5 consists of 16 events strongly associated with the development of post-traumatic stress symptoms.

#### Primary care post-traumatic stress disorder screen for Diagnostic and Statistical Manual of Mental Disorders, 5th edition

The primary care post-traumatic stress disorder (PTSD) screen for Diagnostic and Statistical Manual of Mental Disorders, 5th edition (PC-PTSD-5) is a self-report 5-item questionnaire used to identify individuals with probable PTSD. The screener begins with a question to assess whether the respondent has had any exposure to traumatic events. If a respondent denies exposure, the PC-PTSD-5 is completed with a score of 0. If a respondent indicates a trauma history—experiencing a traumatic event over the course of their life—the respondent answered 5 additional yes/no questions about how that trauma has affected them over the past month. Respondents can score 0 to 5. The PC-PTSD-5 was validated in a large sample of Veterans Affairs primary care patients [23].

#### General Self-Efficacy Scale

The General Self-Efficacy Scale (GSE) is a 10-item self-report measure of self-efficacy. The GSE is positively correlated with optimism and work satisfaction and negatively correlated with depression, stress, health complaints, burnout, and anxiety [24]. The total score ranges between 10 and 40, with a higher score indicating greater self-efficacy.

#### The Pittsburgh Sleep Quality Index

Sleep quality was assessed with the Pittsburgh Sleep Quality Index (PSQI). The PSQI is a validated scale used to assess duration of sleep, sleep disturbance, sleep latency, daytime dysfunction due to sleepiness, sleep efficiency, overall sleep quality, use of hypnotics, and total sleep quality index [25]. The PSQI is composed of 19 items and is scored from 0 to 21 (sum of 7 component scores from 0 to 3); higher scores represent greater sleep difficulties.

#### Connor-Davidson Resilience Scale

Resilience was assessed with the Connor-Davidson Resilience Scale (CD-RISC), which has been validated to assess resilience in general and clinical populations [26]. The CD-RISC is composed of 25 items and is scored from 0 to 100; higher scores represent higher levels of resilience.

#### Profile of Mood States 2nd Edition–Adult

Mood was assessed with the Profile of Mood States 2nd Edition–Adult (POMS 2-A), a widely used psychological inventory of mood states [27]. Volunteers rated 65 mood-related adjectives describing how they felt over the past week, which were used to generate 6 factor-analytically derived subscale scores (tension, depression, anger, vigor, fatigue, and confusion) as well as a total mood disorder score. Higher scores indicate greater mood disorder. This questionnaire was completed while participants were in a fasted state to minimize the acute effects of dietary intake, caffeine, and nicotine on mood.

#### Dimensional Obsessive-Compulsive Scale

Obsessive-compulsive disorder (OCD) symptom severity was assessed using the Dimensional Obsessive-Compulsive Scale, a 20-item self-report instrument that assesses the OCD symptom severity along the following 4 dimensions: contamination; responsibility for harm and mistakes; incompleteness/symmetry; and unacceptable (taboo) thoughts [28].

#### Injury Questionnaire

Volunteers were asked to report musculoskeletal injuries incurred in the last 6 mo. For each injury, they were asked the type, location, side of the body, date of injury, severity of injury, cause of injury, and duration of the injury.

#### The Pain, Enjoyment of Life, and General Activity Scale

The Pain, Enjoyment of Life, and General Activity (PEG) scale is a brief, 3-item, participant-reported pain outcome measure derived from the Brief Pain Inventory [29]. The PEG scale includes 3 questions assessing pain intensity and functional interference (i.e., interference with enjoyment of life and general activity). The PEG scale is scored by averaging the 3 items; scores range from 0 to 10.

#### Twenty-four hour dietary recall assessment

Twenty-four hour dietary recalls were collected using Automated Self-Administered 24-Hour Dietary Recall (ASA24) (https://epi.grants.cancer.gov/asa24/), providing estimates of macronutrient (protein, carbohydrate, and fat) and micronutrient (vitamins and minerals) intake. ASA24 is a validated and standardized web-based tool that assesses food, beverage, and dietary supplement consumption in the previous 24 h. ASA24 is automated and self-administered and allows individuals to record what food and dietary supplements they consumed without the assistance of an interviewer, thereby minimizing respondent bias. This study collected one ASA24 dietary recall at the in-person visit and a second 24-h dietary recall 3 to 10 d later electronically via a personal device.

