Post-stratification survey weights were applied to align the analytic sample with the demographic composition of the active-duty Army population based on sex, race/ethnicity, and rank. Although these weights do not explicitly account for site-based recruitment, they help mitigate potential bias to the extent that differences across installations are reflected in these characteristics. In addition, active-duty Soldiers routinely relocate between installations approximately every 3 to 4 y, resulting in broadly similar demographic distributions across sites. Steps to minimize sampling bias included geographic dispersion of installations, broad recruitment strategies at each site, and balanced enrollment targets across installations (∼100–150 participants at each site).

Interested Soldiers attended an in-person briefing to learn about the study and, if still interested in participating, signed the informed consent before any data collection. The study inclusion and exclusion criteria are shown in Table 3. After signing the informed consent, volunteers are asked to complete a screening questionnaire to obtain demographic information (i.e., sex, age, race/ethnicity, rank/grade, area of assignment, military occupational specialty, and duration at current duty station). Volunteers were then given instructions (i.e., no alcohol for 48 h, no exercise or caffeine for 12 h, no food or beverages except water for 10 h, and no tobacco or nicotine products in the morning before the visit) and scheduled for 1 in-person visit (∼4 h) where outcome measures were assessed (see below). A stool sample kit was provided to volunteers so they could collect the sample at home and bring it to the study visit. Volunteers were also provided with a bag to carry their dietary supplements and medications to the study visit. A subset of volunteers received an actigraph watch to monitor sleep and physical activity to wear until their in-person visit (∼4–7 d after the briefing visit).

**TABLE 3 tbl3:** Inclusion and exclusion criteria for the Military Health and Nutrition Examination Study

Inclusion criteria	Exclusion criteria

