#### Anthropometrics

Body weight was assessed in the morning (06:30–11:00), after an overnight fast, after first toilet use, and in light clothing using a bioelectrical impedance device (InBody 770; InBody USA). Height was measured in duplicate to the nearest 0.1 cm using a stadiometer (Seca; Creative Health Products).

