### Compensation

Participants received $400 for completing data collection during off-duty hours, because they cannot be compensated for research conducted during duty hours. This amount is prorated: $250 for completing the in-person visit, $50 for bringing medications and dietary supplements to the visit for tracking, $50 for collecting a stool sample, and $50 for completing the second dietary recall 3 to 10 d after the in-person visit.

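### Both 24-h recalls are timed from the visit and the stated weights are demographic only, so the weekday/weekend mix of recalled days is uncontrolled, in an unknown direction

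*Protocol article*

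**What the plan says.** The section on the 24-hour dietary recall fixes the timing: "This study collected one ASA24 dietary recall at the in-person visit and a second 24-h dietary recall 3 to 10 d later". The tool covers food, beverage and "dietary supplement consumption in the previous 24 h". The second recall is completed "electronically via a personal device", away from the study site. No rule on day of week is given for either recall.

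Three statements restrict when visits could take place:
- Study population and trial design: participants take "no food or beverages except water for 10 h" before a single visit of about 4 h.
- Anthropometrics: "Body weight was assessed in the morning (06:30–11:00), after an overnight fast".
- Compensation: "Participants received $400 for completing data collection during off-duty hours, because they cannot be compensated for research conducted during duty hours".

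On weighting, Study population and trial design says "Post-stratification survey weights were applied to align the analytic sample with the demographic composition of the active-duty Army population", and names sex, race/ethnicity and rank as the variables. Statistical analyses says only that survey weights will be applied. It lists means and percentages beyond dietary cut-offs among the outputs.

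**The concern.** Mean intakes and percentages beyond the dietary reference values are meant to describe Army Soldiers over an ordinary week. That requires the recalled days to reflect the calendar, about five weekdays to two weekend days, or the analysis to restore that mix.

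Here the recalled days follow from the visit days. A fasting morning block of about 4 h, with payment only for off-duty time, is unlikely to be filled evenly from Monday to Sunday. Weights built on sex, race/ethnicity and rank align who was sampled, not which days were sampled. If intake differs between weekdays and weekend days, the resulting bias does not shrink with sample size. The Introduction wants these data to guide dietary modification and ration formulation, so the mix of days matters for their use.

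**Working it through.** **Inputs from the article.** Recall 1 is completed on visit day v and describes the previous 24 h, so mainly day v − 1. Recall 2 is completed on one of days v + 3 to v + 10. The weights use sex, race/ethnicity and rank.

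**Assumptions.** The article does not give the weekdays of visits, the completion days of recall 2, or the weekday/weekend difference in intake. I assume that recall 2 is completed evenly over its window, that everyone completes both recalls, and that intake differs by 5–15% of the mean between day types.

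**The plan's own figures.** It gives none for the mix of days. The accuracy of 1–3% for percentages not meeting the calcium and vitamin D requirements (Sample size estimation) comes without prevalences or a confidence level. It can be neither confirmed nor refuted, and this point does not depend on it.

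**Step 1, calendar share.** Saturday + Sunday = 2/7 = 28.6%.

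**Step 2, recall 2.** It describes days v + 2 to v + 9. These eight consecutive days contain every weekday once, and the weekday of v + 2 twice. The weekend share is therefore 3/8 = 37.5% for Thursday or Friday visits and 2/8 = 25.0% for all others.

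**Step 3, recall 1.** A Saturday visit describes mainly Friday (weekend share 0%). A Sunday visit describes Saturday and a Monday visit describes Sunday (100%). Tuesday to Friday visits describe weekdays (0%).

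**Step 4, pooled share** = (recall 1 share + recall 2 share)/2. Shift = pooled share − 28.6%. Bias in the mean = |shift| × 5–15%.

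| Assumed visit days | Recall 1 | Recall 2 | Pooled | Shift (points) | Bias in mean |
|---|---|---|---|---|---|
| Saturday only | 0% | 25.0% | 12.5% | −16.1 | 0.8–2.4% |
| Tuesday–Friday equally | 0% | 31.3% | 15.6% | −12.9 | 0.6–1.9% |
| Monday–Friday equally | 20.0% | 30.0% | 25.0% | −3.6 | 0.2–0.5% |
| All seven days equally | 28.6% | 28.6% | 28.6% | 0 | 0 |
| Saturday and Sunday equally | 50.0% | 25.0% | 37.5% | +8.9 | 0.4–1.3% |
| Sunday only or Monday only | 100% | 25.0% | 62.5% | +33.9 | 1.7–5.1% |

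For example, Monday to Friday: recall 1 = 1/5 = 20.0%; recall 2 = (3 × 25.0 + 2 × 37.5)/5 = 30.0%; pooled = 25.0%.

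**Step 5, scale for cut-off percentages (illustration only).** Assume normal intake with a coefficient of variation of 30%. A 2% shift in the mean moves the percentage below a cut-off at the median by 0.399 × 0.02/0.30 = 2.7 points. Where 10% fall below the cut-off, it moves by about 1.2 points. Both are of the same order as the 1–3% accuracy claimed.

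**The case against.** The strongest objection is that this is a condensed article. Day-of-week scheduling, recall-day weights and day-type covariates may sit in the full protocol or analysis plan, which is not shown. The article makes no claim of a balanced mix, and its mention of survey weights rules out nothing further. This stands as a limit on confidence. But the article does name the variables behind its weights, and weights built on those variables cannot correct the mix of days.

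A second objection is that recall 2 is remote and its window covers every day of the week, so it is close to balanced if completion is even. That also stands. The imbalance comes mainly from recall 1, and recall 2 dilutes it without removing it.

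A reader might go further and infer that off-duty days are over-represented because payment is tied to off-duty hours. The article does not support this:
- Recall 1 looks back 24 h, so a Saturday visit, or one on the first morning of leave, describes mainly a duty day.
- Visits in duty hours are unpaid, but nothing excludes them.
- Off-duty and weekend are different classifications, and payment status concerns the visit day, not the recalled day.

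The table shows that the weekend share can move either way.

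**Conclusion.** The point holds as a design and analysis weakness of unknown sign. Both recalls are anchored to the visit, visit days are unlikely to be even over the week, and the weights as described leave the weekday/weekend mix uncorrected.

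The size depends on visit days that the article does not give. For visits spread over Monday to Friday the bias is small. It becomes material only if visits cluster on particular days, above all Sunday or Monday. All visit-day scenarios and the 5–15% intake difference are assumptions, as are even completion of recall 2 and full response. If second recalls are missing, the more variable share from recall 1 counts for more. If the observed mix proves close to 5:2, reporting it settles the matter.

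**What to change.** Collection has ended, so the remedy lies in the analysis:
1. Derive the day of week of each recalled day from the recall date. The article does not say that these dates are stored, but a window of 3 to 10 d cannot be run without them.
2. Report the distribution of recalled days for recall 1 and recall 2 separately.
3. For dietary intake estimates, multiply the survey weight by a day-of-week factor so that weekdays carry 5/7 and weekend days 2/7. Collapse demographic strata where cells are sparse.
4. Include day type as a covariate in dietary intake models.

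This restores the weekday/weekend mix only. It does not restore the duty/off-duty mix, and the text should say so.

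The cost is one derived variable, some wording and larger standard errors. If s is the observed weekend share, and recall days are treated as independent, the variance grows by about (2/7)²/s + (5/7)²/(1 − s). For s = 25.0% this is 0.327 + 0.680 = 1.007, so standard errors rise by about 0.3%. For s = 37.5% it is 0.218 + 0.816 = 1.034, or about 1.7%. Only at the extreme of s = 62.5% is the cost large: 0.131 + 1.361 = 1.491, or about 22%. That is also where the uncorrected bias is largest.
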